##### Physical fitness

The fitness assessments include two items (handgrip strength and standing long jump) from the Assessing FITness in PREschoolers (PREFIT) test battery [137] and one item (Supine Timed Up and Go) from the SUNRISE study [136]. The PREFIT tests, adapted from the Assessing Levels of Physical Activity field-based fitness tests for the assessment of health-related physical fitness in children and adolescents, have shown good reliability in young children [138–140]. A hand dynamometer with adjustable grip will be used to measure hand grip strength (TKK 5001 Grip A, analogue model [141], measurement range 0–100; Takey, Tokio Japan), applying a grip‐span of 4.0 cm [142]. The mean of the best of two trials for each hand will be used. Standing long jump, instructing children to jump as far as possible with both feet together, will be used to measure lower body explosive strength. The best of two trials will be used. Speed-agility will be assessed using the Supine Timed Up and Go test, where children is instructed to lie on their back with their feet on a line, get up as quickly as possible on ‘Go’, run 3 m, to a wall and touch it and return to cross the start line. The best of two trials will be used.

##### Anthropometry and demography

Body weight to the nearest 0.1 kg will be measured using an electronic scale (Seca 899, SECA GmbH, Hamburg, Germany). Height to the nearest 0.1 cm will be measured with a portable stadiometer (Seca 217, SECA GmbH, Hamburg, Germany). Body mass index (BMI, kg/m^2^) will be calculated based on the criteria proposed by Cole et al. [143] and children classified as normal weight (including underweight), overweight, or obese. Demography will be measured by parent questionnaires and includes socioeconomic status (parents’ education and income), children’s, parents’, and grand parents’ origin, children’s birth weight, parents’ weight status and parents’ PA.

##### Sleep

We will assess children’s sleep using 24-h accelerometry and a parent questionnaire. From accelerometry, we will estimate sleep using an algorithm developed and validated to identify sleep/bedrest from waist-worn triaxial accelerometers in 3–6-year-old children [144]. First, the *PhysicalActivity* (v0.2.4) R package is used to remove non-wear periods, defined as ≥ 90 min of consecutive zero counts allowing 2 min of interruptions. Second, the *PhysActBedRest* (v1.1) R package is used to determine sleep using vector magnitude data at 60 s epochs [144]. This algorithm has good sensitivity (0.94), specificity (0.97), and accuracy (0.95) as compared with visual identification of accelerometry-measured sleep periods. In the questionnaire, used in the Sunrise study [136], parents report children’s sleep duration including nap time, when they go to bed and when they wake up, and the consistency of these patterns. Children’s sleep quality is rated on a 1–7 scale.

##### Social-emotional health and self-regulation

To assess social-emotional health, teachers will complete the one-sided Strengths & Difficulties Questionnaire (SDQ, 4–17 years) for each child to provide a brief measure of children’s psychosocial strengths and problems. The SDQ asks about 25 attributes (10 positive, 14 negative, and 1 neutral) and includes five subscales (five items each): *1. Emotional Symptoms Scale; 2. Conduct Problems Scale; 3. Hyperactivity Scale; 4. Peer Problems Scale;* and *5. Prosocial Scale*. Scales 1–4 can be summed to provide a total difficulties score. SDQ uses a 3-point Likert scale (“not true”, “somewhat true” or “certainly true”) to indicate to which extent each attribute applies to each child [145, 146]. The construct validity of the teacher version of SDQ for young children has been demonstrated in several studies [147–150] and has been shown to have better internal consistency and test–retest reliability than the parent version for kindergarten and school children [147, 148].

Self-regulation will be assessed by a structured observation of a child’s performance on the Head-Toes-Knees-Shoulders Revised (HTKS-R) task [151], which includes a downward extension of the original HTKS [152]. The test assesses to which extent a child can use and integrate executive functions to control actions, pay attention and remember instructions [153–156]. To respond correctly, children must listen to instructions, remember and execute gross motor movements according to directions, and inhibit pre-potent incorrect responses. In the first part (10-items), the command “touch your head” requires the children to touch their toes and vice versa, while in the second part (10-items) the command “touch your shoulders” requires the children to touch their knees and vice versa [153]. If a child reach a minimum of 4 points on both levels (2 points are given for a correct response, and 1 point for a self-corrected response), they will be given a third part (10-items), where the paired rules are switched (i.e., head pairs with knees and shoulders pairs with toes) [152]. The HTKS-R also includes a Part 0, where children are asked to say (instead of doing) the opposite of what is instructed [151]. Predefined instructions will be given verbally, without feedback on responses. To familiarize with the test several practice trials are provided at each level [155]. The HTKS is easy to administer, requires few materials and has shown construct validity in European samples [154]. Self-regulation will be scored as the sum of correct (2 points) and self-corrected (1 point) responses over the four parts (range 0–118 points). The project group translated the HTKS-R form to Norwegian.

##### Early academic performance

We will use “*The Expressive Vocabulary”* for language development [157] and *“The Numbers task”* for early math skills [158], both iPad tasks from the Early Years Toolbox, as proxies for early academic performance. Both tasks have shown good convergent validity and reliability. The Expressive Vocabulary task includes 55 items where children are asked to verbally produce a correct label for depicted nouns and verbs. The administrator records the responses (correct/not correct) in an iPad app. In cases of an incorrect response, the administrator will ask children “what else might this be called” until a correct response is given or that the child is unable to produce the target word is indicated. The test will stop if children provide six consecutive incorrect responses. Expressive vocabulary will be scored as overall accuracy [157].

The Numbers task includes 79 items covering numerical concepts (e.g., many), spatial and measurement concepts (e.g., tallest), counting subset (e.g., counting dogs interspersed with cats), matching digits and quantities (e.g., understanding the correspondence between: spoken number *two*, the digit *2*, and its corresponding quantity), number order (e.g., identifying the missing number in a number line), ordinality (e.g., identifying higher/lower numbers), cardinality (e.g., identifying what is 1 st, 2nd, etc.), subitizing (e.g., a rapid appraisal of quantities as having more or less), patterning (e.g., identifying and completing a pattern), and numerical word problems and equations. Children respond by tapping the iPad screen or verbally answering questions in the app. The app includes automated start rules based on the age of the child. The test will stop if children provide five consecutive incorrect responses. Early math skills will be scored as overall accuracy [157].

##### Playfulness, explorative behaviour and well-being

Each of the constructs playfulness, explorative behaviour and well-being will be measured by 7 items using the “Children’s Involvement and Well-being in Movement, Play and Exploration Questionnaire”, developed in this project. A brief description of its rationale, development and evaluation is provided in Sect. "Development of measures of movement competence, creativity, playfulness, explorative behaviour and well-being in young children.". Kindergarten staff will be asked to score the child’s observed behaviour within the past month to capture how children generally behave and will avoid any specific events which may have an impact on the child. The child will be scored for each statement on a 5-point Likert Scale from “never” to “almost always”. Scores are summed for each construct or scored alternatively, given the instrument's construct validity. More details about the instrument, scoring procedures and measurement properties will be published later.

#### Analysis plan

##### Primary aim

To test the study’s effectiveness, the main analyses will employ an intention-to-treat principle, including all participants and kindergartens originally allocated to their respective groups [159, 160]. To study efficacy, secondary analyses will be limited to kindergartens that exhibit acceptable intervention adherence. We will seek to minimise missing data [161]. To allow for investigation of missing data mechanisms and thus assumptions underlying the statistical analyses, we will provide a detailed account of reasons for missing observations using suitable flow charts [81]. We will include attrition analyses to investigate whether missing data are related to child characteristics. In the analyses, missing data will be handled using linear mixed models or structural equation modelling (SEM) [162–165].

We will determine intervention effects by testing for time*group interactions adjusted for baseline levels of the outcome [166]. We will account for the cluster effect of participant and kindergarten using linear mixed models [167] (or generalized linear mixed models, dependent on distributions) or multilevel SEM for mediation analyses [164, 168]. The primary analysis will not be adjusted for covariates (beyond baseline levels of the outcome), while the per-protocol analysis will be adjusted for differences between groups, as appropriate.

Interpretation of study effects will be based on p-values (i.e., a p-value ≤ 0.05 is considered statistically significant), effect sizes and patterns of effects across variables; the latter will be considered of greatest importance when drawing study conclusions. Consistent with this approach, p-values will not be adjusted for multiple testing. Main analyses will be performed using IBM SPSS v. 30 or later versions (IBM SPSS Statistics for Windows, Armonk, New York: IBM Corp., USA) and MPLUS v. 8 or later versions (Muthén and Muthén, Los Angeles, USA). Reporting will be guided by the CONSORT statement [81, 169].

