**Fig. 2 Fig2:**
[figure not shown]
Flow chart and timeline of the MoveEarly cluster RCT study

We will cluster randomize participants at the center level since we regard delivery of the intervention on the center level the only practical approach to avoid contamination. An independent researcher will randomize 50 kindergartens to the intervention group (25 kindergartens) or the standard of care control group (25 kindergartens), with stratification on the two kindergarten owners. Randomization will be performed using a simple random number generator (SPSS) and a 1:1 ratio for the 2 intervention arms when the list of participating kindergartens, sorted alphabetically for each owner, is complete. The list of centers allocated to each group will be handled by the primary investigator. The primary investigator will inform kindergarten directors about their group after completing recruitment of children. Blinding of participants and kindergartens is not possible due to the nature of the experiment. However, we expect that children will not be aware of their group assignment. To limit potential biases, the fewest possible researchers and assessors involved in project management, data collection, and statistical analysis will have knowledge about the group assignment and the study hypotheses.

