#### Samples and methods

The process evaluation will draw on multiple methods to triangulate data and user perspectives [78] and includes four samples. The first sample includes all kindergartens participating in the study (i.e., both intervention and control), the second sample includes all intervention kindergartens, the third sample includes selected kindergartens invited to take part in a multi-site case study (i.e., both intervention and control), and the fourth sample includes only the intervention kindergartens taking part in the multi-site case study. While the research including all kindergartens will test between-group effects and describe implementation measures in the MoveEarly intervention, the multi-site case study will use an ethnographic approach to provide an in-depth understanding of how the intervention evolves and builds momentum in kindergartens [195]. An overview of the methods and timelines for the data collection in the process evaluation is provided in Fig. 5.

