##### Sample 2: Intervention kindergartens

Data collection in sample 2 includes written work by staff submitted as part of the professional development, registration of adherence to the professional development, multiple short implementation questionnaires and a project evaluation questionnaire. Contact points between researchers and kindergartens will be logged.

Several types of written work (project plans, reflection papers and project reports) will be collected from the kindergarten internal project group to assess the visibility and formalisation of the MoveEarly intervention in the intervention kindergartens. Project plans will include each kindergartens’ own aims for the development work, the planned approach to integrate the MoveEarly pedagogical principles into their daily practice (e.g., whether principles and/or activities will expand, extend and/or enhance children’s opportunities [84]) and a description of the organization of the process, including milestones, leadership and responsibilities. Reflection papers will include a discussion about children’s and staff’s experiences with the move-play-explore pedagogy in relation to the pedagogical principles based on plans, videos, pictures and/or observations. Project reports will include staff’s reflections regarding their experiences of successes and challenges during implementation of planned aims, pedagogical approaches and institutional organization, with the overarching aim of developing action points for improved future practices.

Adherence to the professional development will be registered throughout the intervention period. These data will include attendance to all physical and digital meetings and submitted written work. Additionally, researchers will score each kindergarten on a 5-point Likert scale in terms of the 1) director’s and project group’s leadership and 2) staff engagement. Primary focus areas will be level of concretization of tasks, plans and milestones in written work and meetings, and involvement of all staff members in implementing the intervention.

The kindergarten project group will complete multiple short questionnaires to rate their experience of collaboration with researchers, resources provided them, and implementation of the intervention in their kindergarten, at all physical seminars except for the kick-off. Questions will be tailored on each occasion according to formal and informal feedback from kindergartens during the project period.

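### The efficacy analysis selects intervention kindergartens on adherence recorded after randomisation and, on the natural reading, compares them with unselected controls; baseline adjustment reduces the bias but cannot be relied on to remove it

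*Protocol article*

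**What the plan says.** Under Outcome evaluation, Analysis plan, Primary aim, the protocol article makes intention-to-treat the main analysis: "the main analyses will employ an intention-to-treat principle, including all participants and kindergartens originally allocated to their respective groups". It then adds the secondary analysis: "To study efficacy, secondary analyses will be limited to kindergartens that exhibit acceptable intervention adherence". Later in the same section this is called per-protocol and given a covariate rule: the primary analysis adjusts only for the baseline outcome, "while the per-protocol analysis will be adjusted for differences between groups, as appropriate".

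Adherence is described in the process evaluation under Sample 2. Samples and methods defines that sample: "the second sample includes all intervention kindergartens". On timing: "Adherence to the professional development will be registered throughout the intervention period". On content: "These data will include attendance to all physical and digital meetings and submitted written work". In addition, "researchers will score each kindergarten on a 5-point Likert scale in terms of the" leadership shown by the director and project group, and of staff engagement. Under Timeline, randomization and blinding, an independent researcher will "randomize 50 kindergartens to the intervention group (25 kindergartens) or the standard of care control group (25 kindergartens"), stratified on the two owners.

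**The concern.** Randomisation makes the two sets of 25 kindergartens comparable. Dropping intervention kindergartens because of what they did afterwards undoes this. Controls have no programme to attend and no written work to submit, so they cannot be selected in the same way. Kindergartens that attend, write and engage plausibly have better leadership, steadier staffing and more motivation, and these may help children whatever the programme does.

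The result would be reported as efficacy while mixing the programme effect with the kind of kindergarten able to follow it. The likely direction favours the intervention. Primary aim gives most interpretive weight to patterns across outcomes and makes no multiplicity adjustment. Selection on kindergarten quality would tend to move several outcomes the same way, which is the pattern the plan treats as evidence.

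**Working it through.** **Inputs from Sample, sample size calculations and recruitment:** ICC 0.05 to 0.10; 9 children per cluster; coefficient of variation of cluster size 0.65; correlation of repeated measurements r = 0.60 to 0.70; detectable effects 0.25 to 0.40.

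**Assumed, because the article gives neither:** the share of intervention kindergartens kept, p, and the correlation ρ between adherence and the kindergarten-level outcome.

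**1. The plan's own figure.** Design effect = 1 + ((CV² + 1)m − 1) × ICC = 1 + (1.4225 × 9 − 1) × ICC = 1 + 11.8025 × ICC. This gives 1.59 at ICC 0.05 and 2.18 at ICC 0.10, against the stated 1.60 to 2.19. The inputs are consistent.

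**2. Bias without baseline adjustment, true effect zero.** Kindergarten effects have SD √ICC. Keeping the top share p on adherence shifts their mean by √ICC × ρ × φ(z)/p, where z is the truncation point. For p = 0.60, φ(z)/p = 0.644.

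| ICC | ρ = 0.3 | ρ = 0.5 | ρ = 0.7 |
|---|---|---|---|
| 0.05 (√ = 0.224) | 0.043 | 0.072 | 0.101 |
| 0.10 (√ = 0.316) | 0.061 | 0.102 | 0.143 |

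The range is 0.04 to 0.14 SD.

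**3. Bias after baseline adjustment, if quality shifts baseline and follow-up equally.** The selected group is then ahead by the same amount at both times. Adjustment with slope b removes b times the baseline lead and leaves (1 − b) of the bias. Taking b ≈ r:
- smallest: 0.043 × (1 − 0.70) = 0.013 SD
- largest: 0.143 × (1 − 0.60) = 0.057 SD

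Simulation of this model (15 of 25 intervention kindergartens kept, 25 controls, 9 children each) agrees: about 0.01 to 0.06 SD.

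**4. If quality also affects growth.** Less is removed. Suppose the correlation r applies at kindergarten level and adherence correlates ρ with what baseline leaves unexplained. The factor is then √(1 − r²), which is 0.71 to 0.80, and the range is 0.043 × 0.71 = 0.03 to 0.143 × 0.80 = 0.11 SD.

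**5. Sensitivity to the share kept.** At p = 0.80, φ(z)/p = 0.35. Unadjusted bias runs from 0.224 × 0.3 × 0.35 = 0.02 to 0.316 × 0.7 × 0.35 = 0.08 SD. On the step 3 assumption it falls to 0.02 × 0.30 ≈ 0.01 and 0.08 × 0.40 ≈ 0.03 SD. With ρ = 0 there is no bias.

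**6. Error rate.** In simulated trials without baseline adjustment, 60% kept and ρ 0.3 to 0.8, the two-sided type I error was 0.062 to 0.20. A test keeping all 50 kindergartens stayed at 0.048 to 0.054. The first range overstates the planned, baseline-adjusted analysis; the second shows what keeping the randomised groups protects.

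**The case against.** The strongest reply has five parts.

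- **Kindergarten quality is measured in both arms.** A reader might infer that controls have no such data. The article does not support that. Under Sample 1, directors of all kindergartens complete a baseline questionnaire on leadership and organisation, and pedagogical leaders complete a 25-item self-assessment of environment and pedagogy. Adjustment could use these. This stands. However, Primary aim does not name them as covariates, and programme adherence and the researchers' engagement rating have no control counterpart.
- **The unadjusted range overstates the bias.** Effects are to be adjusted for baseline levels of the outcome. This stands, and steps 3 and 4 allow for it.
- **The milder case has support.** The Feasibility study reports good implementation, and kindergartens facing exceptional difficulty are excluded beforehand. This favours a high share kept and a small bias, but does not establish it.
- **Two links are inferred.** The article does not say that all controls are kept, although a between-group comparison is planned and controls have no adherence record. Nor does it say that the leadership and engagement ratings define acceptable adherence; they are listed in addition to attendance and written work. Attendance and written work alone would still select on capacity.
- **The analysis is secondary, and details may sit elsewhere.** A cut-off and covariate list commonly belong in an analysis plan that is not shown, so their absence is no finding. But no cut-off removes selection after randomisation.

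**Conclusion.** The point holds in a limited form. By its stated rule, the efficacy analysis selects on a post-randomisation variable that exists in one arm only. Its estimate should not be presented as the effect of the programme when followed. On the assumptions of 60% kept and ρ of 0.3 to 0.7, the spurious effect is about 0.04 to 0.14 SD unadjusted. It is about 0.01 to 0.06 SD after baseline adjustment if quality shifts both time points equally, more if quality affects growth, and small if most kindergartens adhere. Against detectable effects of 0.25 to 0.40, this is a moderate distortion of a secondary result. The intention-to-treat analysis is sound.

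A reader might also conclude that a complier-average analysis should simply replace the restricted one and would be unbiased. The article does not support that either. Kindergartens below a cut-off are still offered seminars, visits, the online resource and a contact researcher, so the assumption of no effect below the cut-off is doubtful. For illustration, let 60% adhere with effect 0.30 and 40% partly adhere with effect 0.15. Intention-to-treat is 0.6 × 0.30 + 0.4 × 0.15 = 0.24, and the complier-average estimate is 0.24 / 0.6 = 0.40 against a true 0.30.

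**What to change.** 1. Keep the restricted comparison if wanted, but call it descriptive, not efficacy. Replace the open-ended adjustment with pre-specified baseline covariates available in both arms: baseline outcome, owner, and the Sample 1 baseline questionnaires on leadership and pedagogical practice.
2. Estimate the adherence effect by a complier-average causal effect analysis on all 50 randomised kindergartens. Use randomised arm as instrument and clustering on kindergarten. Define adherence by attendance plus written work, with the cut-off fixed before allocation is opened at database lock.
3. Report that estimate as a possible upper bound, with a sensitivity analysis using a lower cut-off or continuous adherence.

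Cost: revised wording, one further model and its sensitivity analysis, and no new data. The interval is wider: at 60% adherent, roughly 1/0.6 = 1.7 times the intention-to-treat interval if the adherent share is treated as fixed. The assumption of no effect below the cut-off must be stated openly.
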